**4.3.2 - Data Collection and X-ray Ordering**

**4.3.2.1 - Patient Entry**

Every blunt trauma victim presenting to a study center will undergo a clinical evaluation. The examining physician will determine if computed head tomography is indicated, using whatever criteria they deem appropriate. Physicians will be informed that it is not currently possible to exclude intracranial injuries in patients who present with any of the risk criteria, and they will be encouraged (but not required) to obtain radiographic imaging on any blunt head trauma victims presenting with one or more of these criteria (see Appendix - B for a sample data entry screen and listing of criteria). Conversely, the clinicians will also be informed that the criteria have yet to be proven reliable, and that imaging should be considered for any patient suspected of harboring an intracranial injury. There will be no formal requirement to obtain or exclude tomographic imaging of any patient. Physicians will be free to order or omit computed head tomography at their discretion.

Data capture will occur each time a request for computed head tomography is made. Tomographic imaging will be performed only after a computer generated radiographic request is presented to the tomography technician. Tomographic requests will not be available until the examining physician completes a full assessment and records the survey responses. This strategy assures that a complete data set will be captured on each patient prior to radiographic imaging. Several of the participating sites use computer based automated entry systems to order radiographic imaging. Previous experience reveals that these systems can be easily modified to adhere to our study protocols, including the collection and de-identification of survey data and imaging results. Because these systems are automated, they do not print imaging requests, but can be programmed to issue requests only after survey data has been entered. Our two prior studies reveal that these systems are easily configured, very reliable, and easier to maintain than standard systems using printed requests.

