Because computer generated requests will be required for all emergency department head tomographs, patients who present with non-traumatic indications may be enrolled in the study. Physicians will be required to indicate the non-traumatic nature of these evaluations. To assure compliance with the methods of this proposal, clinicians will still be required to enter relevant study information. This information will be retained in a separate database, and will be analyzed separately from data on blunt head injury victims. This information may be useful in developing selective indications for non-traumatic computed head tomography. However, this information is not relevant to the hypotheses being tested in this study.

Imaging requests may be generated prior to complete data entry in physiologically unstable patients. Clinicians will ultimately complete data entry in these patients, but complete data entry may occur after computed head tomographs have been reviewed. In such cases, the data entry for the case will document the physiologic instability and non-concurrent nature of the data collection. In our previous study, clinicians classified 8.7% of patients as unstable (including 17.5% of patients with intracranial injuries), but were able to complete assessments on all patients. In this regard, the study protocol allowed clinicians to provide expeditious care to even the most severely injured patients, while having a negligible impact on data collection.

Data will be collected on all blunt head injury victims entered into the study. Inclusion will not depend on age, sex, race or ethnic origin. Specific information regarding race will be collected to determine what effect, if any, race may have in evaluating patients for risk of injury. Demographic analyses will be performed on age and sex data. Study sites (Appendix A) have been selected to represent a broad spectrum of medical environments. These sites are expected to enroll a diverse population containing all races and both sexes. All sub-populations will be represented in the study in the same proportions as they present with blunt head injuries.

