**4.3.10.3 - Duration of the study**

The study duration will be determined by the following:

The study will terminate if it encounters 10 cases having significant head injury that requires neurosurgical intervention, but labeled “low risk” by the decision instrument. Data collection will otherwise continue until the study enrolls 368 cases requiring neurosurgical intervention (we anticipate this may require as many as 31,000 total blunt head injury cases).

In the unlikely event that the study terminates without validating the clinical decision instrument, the data collected in the study will still be used to provide important information about blunt intracranial injury. This will include information on the demographics of head injury including overall prevalence, geographic and seasonal variations, and distributions by age, race and sex. Tomographic reports will yield important information on the different types of intracranial injuries, including prevalence and distributions among the various demographic groups. This information will be of use in emergency neurological and clinical assessment, and will prove useful in formulating future recommendations. Data on the presence or absence of the criteria in individual patients will be useful in assigning clinical significance to the criteria. This data will be analyzed by regression analysis to identify relationships between intracranial injury and clinical presentation. Such studies can aid in risk assessment and stratification of risk among blunt head injury patients. This information will in turn guide future studies that seek to improve the management of blunt head trauma victims. Finally, the failure to validate the decision instrument is an important finding on its own. It would suggest that clinicians must be extremely careful in evaluating head injury patients and that tomographic scanning may be indicated in many if not most of these individuals.

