**5.8 - Inclusion of children**

The sites participating in the study are expected to enroll a diverse population containing all ages. Children will be enrolled in the study in the same proportions as they present with blunt head injuries. The study poses no special risk to children, and there are no special circumstances that apply to their participation. Study sites have been carefully chosen to insure a broad enrollments and a diverse population. The information collect by the study will be analyzed to determine whether age plays an important role in the identification of blunt head injuries.

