*Persistent vomiting* is evidenced by recurrent (more than one episode), projectile or forceful emesis (either observed or by history) after trauma.

*Coagulopathy* is any impairment of normal blood clotting such as occurs in hemophilia, secondary to medications (Coumadin, heparin, aspirin, etc.), hepatic insufficiency and other conditions.

*Age 65 years or more* is determined by available history.

**Appendix D – Scripted Survey Form for Long-Term Follow-Up of Patients Who Do Not Undergo Tomographic Imaging During Their Initial Evaluation**

*Script for contacting study participants by telephone for long-term follow-up.*

Hello, Mr/s.__________________, my name is __________________. I work with [name] at the UCLA Emergency Medicine Center, and we are working on a research study on head injury. Your participation is completely voluntary. If you don’t mind, I’d like to tell you a little more about the study, and what is involved in participation. Please know that it is your right to decline to participate in this study for any reason, at any time. In addition, whether your decision to participate or not will not affect any aspect of your future medical care.

The study is being done to make sure that patients who have been seen in the emergency room and who do not receive a type of x-ray called a head CT do not have any significant head injury. Your participation in this study would consist entirely of answering a few short questions, which will help us determine if you have had any problems that might have been caused by your head injury after you left the emergency room. We will not record your name or patient number, and your participation would be completely anonymous.

If you have any questions or concerns about your right as a research subject, you may contact the UCLA Office for Protection of Research Subjects. Their phone number is [contact], or you may write then at OPRS, [name].

Would you like to take part in the study?

Do you have any questions or concerns I can address for you about the study?

(If study participant answers affirmatively to participate, then present study related questions as follows:).

Did you return to the hospital or go to another facility after your discharge from the emergency room.

**🞎** Yes **🞎** No **🞎** Unknown

If yes, did you receive any x-rays or imaging studies?

**🞎** Yes **🞎** No **🞎** Unknown

If yes, do you know if you had the following types of x-rays taken?

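### The protocol says sub-populations enter in the proportions in which they present, but the cohort is selected by discretionary CT request, so prevalence and demographic results need a CT-selected label

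*Protocol*

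**What the plan says.** Section 4.3.2.1 (Patient Entry) makes two statements about who is in the study. One is about policy: "Inclusion will not depend on age, sex, race or ethnic origin". The other is about composition: "All sub-populations will be represented in the study in the same proportions as they present with blunt head injuries". The composition statement returns in the sections headed 5.6, 5.7 and 5.8 in the body of the protocol; for example, "Children will be enrolled in the study in the same proportions as they present with blunt head injuries".

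The same section sets the entry mechanism: "Data capture will occur each time a request for computed head tomography is made", and "Physicians will be free to order or omit computed head tomography at their discretion". Physicians are also informed of the instrument's criteria. On imaging, the section adds: "they will be encouraged (but not required) to obtain radiographic imaging on any blunt head trauma victims presenting with one or more of these criteria". Section 1 and Appendix C include age 65 or over among the instrument's criteria. Sections 4.1 and 4.2 define the study population as patients undergoing head CT, and section 4.3.8.3 removes records of patients who had no CT.

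On the outputs, section 4.3.10.3 says of the data if validation fails: "This will include information on the demographics of head injury including overall prevalence, geographic and seasonal variations, and distributions by age, race and sex". Section 5.4 promises the same without that condition. Neither restricts the description to imaged patients.

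**The concern.** A cohort that opens with a CT request is a sample of imaged patients. It reproduces the mix of presenting patients only if every sub-population is imaged at the same rate. The protocol does not assume that, and for age it encourages a difference.

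What is at stake is the label on a set of descriptive results. Overall prevalence, injury frequency by demographic group and the demographic make-up of head trauma all need everyone who presents as the denominator. Taken from this cohort and described as features of head injury, they would partly describe CT-ordering practice. A reader could then take a difference in yield between groups for a difference in injury risk.

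**Working it through.** **1. The plan's own figures.** Section 3.2 uses the exact lower limit with no misses and α = 0.05, taken as α/2. With X = N this is P_L = 0.025^(1/N). N = 368 gives 0.99003 and N = 367 gives 0.989999, so 368 is reproduced. At 1.2% prevalence, 368 / 0.012 = 30,667, which agrees with the stated 31,000 after rounding. Neither figure uses the statement about proportions, so neither changes.

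**2. The passages side by side.**

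| Topic | Representative of presenters | Selected by CT |
|---|---|---|
| Composition | 4.3.2.1 (last paragraph), 5.6, 5.7, 5.8 | 4.1, 4.2, 4.3.2.1 (entry trigger), 4.3.8.3 |
| Acknowledged limits | none in 4.3.10.3 or 5.4 | 4.3.9.2 (sample may not represent trauma patients generally); 4.3.9.3 (population depends on which physicians choose to image) |

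The two columns cannot both hold unless imaging rates are equal across groups.

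**3. Share of a group in the cohort.** Let g be its share among presenters and r its imaging rate relative to everyone else. Its share among imaged patients is g·r / (g·r + 1 − g). The documents give neither quantity. Assuming g = 20% for age 65 or over:

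- r = 1: 0.20/1.00 = 20%, the only case in which the stated property holds
- r = 1.25: 0.25/1.05 = 23.8%
- r = 1.5: 0.30/1.10 = 27.3%
- r = 2: 0.40/1.20 = 33.3%
- r = 3: 0.60/1.40 = 42.9%

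**4. Overall prevalence.** If a fraction q of presenters is imaged and un-imaged patients have no such injury, prevalence among presenters is q times prevalence among imaged patients. Taking 1.2% among imaged patients, q = 75%, 50% and 25% (assumed) give 0.9%, 0.6% and 0.3%.

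**5. Yield by group, and what is not distorted.** Assume two groups of 1,000 presenters, each with 6 surgical injuries (0.6%), all of them scanned. If 600 of one group and 300 of the other are imaged, the yields are 6/600 = 1.0% and 6/300 = 2.0%, a ratio of 2.0 at equal true risk. With 60% and 40% imaged the ratio is 1.5 (1.0% and 1.5%); with 50% and 40% it is 1.25 (1.2% and 1.5%). Among the injured, however, the split remains 6 to 6, as it is among all presenters. So distributions among injured patients are correct if all injured patients are scanned.

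Some support for that condition comes from section 3.1: of 1,266 un-imaged patients followed up in the derivation study, none needed neurosurgical intervention. The exact upper 95% limit for 0/1,266 is 1 − 0.025^(1/1266) = 0.29%, so the condition is supported but not proved.

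**The case against.** The strongest reply is that the sentence closes a paragraph on inclusion policy and recurs under inclusion headings, so it may mean only that no group is excluded or given a quota. No estimator, weight or sample size depends on it. The selection is also disclosed: sections 4.1 and 4.2 define the cohort openly as CT patients, and sections 4.3.9.2 and 4.3.9.3 discuss the consequences. Much of this stands and is why the point is minor. It does not remove it: the policy has its own sentence, the quoted one goes further and asserts composition, and the limitations sections leave 4.3.2.1, 4.3.10.3, 5.4 and 5.6 to 5.8 as they were.

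Second, the mechanism for age is encouragement without obligation, and section 4.3.2.1 does not itself name age; the criterion comes from section 1 and Appendix C. That limits what can be said about size, but not the conflict.

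Third, a reader might infer more than the text supports:

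- That all the demographic results would be wrong. Step 5 shows that distributions among the injured need not be.
- That these results become the study's main product if validation fails. Section 4.3.10.3 lists them beside injury types and regression of injury on presentation, and calls failure to validate a finding in itself.
- That yield will be reported as risk by race, sex or age. Sections 4.3.2.1 and 5.6 to 5.8 speak of each factor's role in evaluating patients or identifying injuries, which may equally mean the instrument's performance by group.
- That sex or race composition is shown to be distorted. No imaging rates by sex or race are given.
- That geographic variation should be dropped because section 4.3.1 names four hospitals. That count alone does not make the case.

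**Conclusion.** The stated representativeness is not a property of this design. For age it conflicts with the imaging guidance given to physicians; for sex and race it is unsupported, and neither the size nor the direction of any departure can be found from the documents. Quantities with all presenters as denominator would be mislabelled if reported as sections 4.3.10.3 and 5.4 describe them.

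The size depends wholly on imaging rates that the documents do not give; the figures above show how it varies and are not estimates. Section 4.3.7 lists sensitivity, negative predictive value and specificity, and the comparison with the Canadian instrument, as the outcomes. Prevalence and demographics are neither primary nor secondary outcomes, and the primary sensitivity analysis is untouched. The text is wrong as written, and the correction is minor.

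**What to change.** 1. In section 4.3.2.1 and sections 5.6 to 5.8, say that sub-populations are represented in the proportions in which they are selected for head CT. The sentence that inclusion does not depend on age, sex, race or ethnic origin can remain as a statement of eligibility policy.
2. In sections 4.3.10.3 and 5.4, label prevalence and demographic distributions as those among blunt head injury patients selected for CT.
3. Add that differences in injury yield by age, sex or race among scanned patients are not to be read as differences in injury risk among all presenters.
4. If imaged patients are compared with un-imaged ones, call the comparison descriptive. At UCLA, section 4.3.3.1 records the demographics of un-imaged patients for a fixed group of 368 who consent; section 4.3.9.2 mentions un-imaged cases at the Pittsburgh site for specificity. Neither gives imaging rates by group without a count of all eligible presenters.

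The changes are to wording only, with no new data and no change to sample size or the main analysis. The cost is that the study's descriptive claims become narrower.

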**4.3.2.2 - Assessing the potential for work-up bias**

It is possible that a patient with a significant head injury could exhibit none of our study criteria *and* not be selected for tomographic scanning. Such a case would represent an undetected false-negative event; all combinations of our criteria would fail, and we would be unaware of the failure. Such cases would create work-up (verification) bias and lead to erroneous estimates of sensitivity and negative predictive value. It is not possible, within reasonable budget limitations, to track all blunt head injury victims for such an occurrence, however, it is possible to tract a screening subset to determine whether false negative events occur and to estimate the potential magnitude of work-up bias. Thus, the presence or absence of each screening criterion and long-term outcome will be determined on a cohort of 368 consecutive blunt head injury patients who present to the Ronald Reagan UCLA Medical Center, but do not undergo CT head imaging.

The clinician caring for these patients will invite them to participate in a long-term outcome study. Research assistants, present in the emergency department on a continuous basis, will contact interested patients (or their caretakers) during their initial visit and obtain informed consent to participate in a structured telephone survey to take place three months after the date of injury. Patients who agree to participate in the study will be asked to provide a preferred time and phone number for the follow-up survey. Patients who do not have phones will be given the option of returning to the emergency department for the survey. Additional details of the work-up bias assessment are included in later sections of this proposal.

**4.3.3 - Data Collected**

Data collected by the study include reason for tomography (blunt trauma, other), patient stability (stable, unstable), date of injury, patient’s date of birth, race and sex. Clinicians will assess each patient for the presence or absence of the following criteria: 1 - signs of basilar, depressed or diastatic skull fracture, 2 - scalp hematoma, 3 - neurological deficit, 4 - abnormal level of alertness, 5 - abnormal behavior, 6 - persistent or forceful vomiting, 7 - coagulopathy. Age will be determined by referencing the patient’s date of birth to determine if they are of age greater than 65 years. Clinicians will also assess the patient’s Glasgow Coma Scale score, whether the patients experienced a dangerous mechanism of injury, or whether the patient exhibited more than 30 minutes of amnesia before impact. Appendix - B contains a sample data collection sheet, and Appendix - C gives precise definitions and instructions for classifying physical findings. Each computer record will also carry embedded information indicating the institution producing the data.

We will prepare special education kits (similar to the ones we used in the previous head injury study) with scripts, slides and overheads to assist site physicians in training their clinicians in our study protocols. The clinicians will be introduced to the candidate criteria by reading the descriptions provided in Appendix - C. We will intentionally avoid exposing the clinicians to any more detailed training regarding the definitions and assessment of the candidate criteria. The rationale for this action relates to the ultimate implementation of our clinical decision instrument. Past experience shows that it is possible to develop and validate clinical decision instruments that have exceptional performance when implemented by specially trained and highly skilled evaluators. These same instruments subsequently exhibit poor performance when implemented by less skilled practitioners in the “real world” [59]. It is our goal to assess the performance of practicing clinicians who have not received special training in criteria assessment, and may have gained an understanding of the decision instrument by reading the medical literature. Thus, we would like to validate our decision rule using physicians who’s exposure to the criteria is similar to that of a physician who might have encountered the instrument while reading the medical literature. This is an approach similar to that used in validating our cervical spine decision instrument, and in the derivation phase of this study. Subsequent evaluations have shown that clinicians can reliably and consistently assess the presence or absence of the criteria [60,61,71].

It is possible that clinicians may not be able to evaluate individual criteria in some patients. For example, it may not be possible to perform a detailed neurological exam and assess motor strength in an individual who has multiple extremity fractures and is unable to cooperate. Clinicians can indicate such occurrences by designating the presence or absence of the individual criterion as “unknown”. The overall decision instrument will treat these “unknown” responses as abnormal responses. Individual risk criteria will be classified as absent only if they can be tested and found to be absent. Consequently, the decision regarding the ultimate need for tomography is based on measuring individual criteria and determining that they are *all absent* in a given individual. If a patient exhibits any of the criteria, or if one or more of the criteria cannot be assessed, the individual will be labeled positive by the decision instrument. Such patients may harbor a significant intracranial injury and should be considered candidates for tomographic scanning. Clinicians are not to use the “unknown” designation in lieu of an adequate evaluation. Our experience with the cervical spine and head injury derivation studies reveals that study physicians use this designation appropriately.

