**Protocol Summary**

**1. SPECIFIC AIMS**

Radiographic imaging can provide information that is crucial in managing victims of blunt trauma. However, liberal and indiscriminant imaging is expensive, can delay critical interventions, and unnecessarily exposes patients to ionizing radiation and its potential for lethal malignant transformation.

Considerable benefit could be realized by identifying clinical criteria that reliably classify the risk of specific injuries in blunt trauma patients. Patients identified as “no risk” by such criteria would not harbor specific forms of injury, and would receive no benefit from radiographic evaluation for such injuries. These patients could safely be spared the expense and radiation exposure associated with such imaging.

The purpose of this project is to identify and validate the use of clinical criteria to stratify the risk of specific injuries among blunt trauma patients. This proposal specifically addresses the use of such criteria in assessing patients for intracranial injuries, where our previous work suggests that a decision instrument, composed of a limited number of clinical criteria, can reliably identify blunt head injury victims who have “no risk” of significant brain injury, and therefore no need for computed head tomography. We estimate that nation-wide implementation of this decision instrument could safely reduce tomographic imaging of blunt head injury victims by more than 12%, and reduce annual radiographic charges by $90 million, while simultaneously expediting trauma care and decreasing radiation exposure and its associated risk of radiation-induced malignancy.

The specific aim of this proposal is reduce computed head tomography by validating the ability of a previously developed decision instrument to reliably identify blunt head injury victims who have no risk of intracranial injury requiring neurosurgical intervention, and who can subsequently be safely spared tomographic imaging. This goal will be accomplished by confirming the following two hypotheses:

I - Blunt trauma victims have no risk of intracranial injury requiring neurosurgical intervention, and hence no need for imaging, if they exhibit all of the following characteristics: 1 - No evidence trauma skull fracture; 2 - No scalp hematoma; 3 - No neurological deficits; 4 - Normal level of alertness; 5 - Normal behavior; 6 - No persistent vomiting; 7 - No coagulopathy; 8 - Age less than 65 years.

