Our work represents the most recent and rigorous attempt to develop a decision instrument for tomographic imaging of blunt head injury patients. By applying recursive partitioning to a prospective cohort of 13,728 blunt head injury victims undergoing tomographic imaging, we found that eight criteria were independently and highly associated with intracranial injury. These criteria included evidence of significant skull fracture, scalp hematoma, neurologic deficit, altered level of alertness, abnormal behavior, persistent vomiting, coagulopathy and age greater than 65 years. These criteria identified clinically important intracranial injuries with 98.3% sensitivity (95% CI: 97.2 – 99.0%), and 99.1% negative predictive value (95% CI: 98.5 0 99.5%). A decision instrument composed of these criteria would have identified 901 of 917 clinically important intracranial injuries. Furthermore, none of the 16 missed injuries required neurosurgical intervention. Application of the decision instrument would have decreased tomographic imaging by 12.9% [65]. As mentioned previously, recursive partitioning alone cannot guarantee that the identified criteria will exhibit acceptable performance when applied to a new cohort. Consequently, the performance of a decision instrument based on these criteria needs to be confirmed by a separate validation study.

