In particular, we propose evaluating the performance of a decision instrument composed of the following criteria: 1 - evidence of significant skull fracture, 2 - scalp hematoma, 3 - neurologic deficit, 4 - altered level of alertness, 5 - abnormal behavior, 6 - persistent vomiting, 7 - coagulopathy, and 8 - age greater than 65 years. Furthermore, while it is not the primary goal of this study, we propose a concurrent evaluation of the Canadian decision instrument composed of the following criteria: 1 - age 65 years or greater, 2 - persistent abnormal GCS scores, 3 - suspected open skull fracture, 4 - any sign of basal skull fracture, 5 - persistent vomiting, 6 - dangerous mechanism of injury, 7 - amnesia before impact > 30 minutes. This additional evaluation entails minimal additional burden for the study, and offers the potential to not only validate decision instruments for tomographic imaging, but also enable us to identify the most optimal strategy in terms of reduced CT usage.

Statistically reliable criteria must exhibit a sensitivity quotient of roughly 368/368 to be 95% certain that the true sensitivity is greater than 99.0% (i.e. to validate the sensitivity at the 99.0% confidence level with 95% certainty, the decision instrument would need to identify 368 consecutive intracranial injuries requiring neurosurgical intervention without any misses). The prevalence of neurosurgically important intracranial injuries among blunt trauma victims is between 1.2% and 1.4% [64, 65], which means that approximately 31,000 patients will be needed to guarantee a sample size large enough to provide the necessary statistical significance [48]. Thus, nearly 31,000 blunt head injury victims will be needed to validate the decision instrument for selective tomographic imaging.

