Phase II - Derivation of Selective Criteria

*Developing a Decision Instrument to Guide Computed Tomographic Imaging of Blunt Head Injury Patients*

[name], PhD, [name], MA, [name], [name], [name], MD, [name]: NEXUS II Investigators.

*J Trauma* 2005;59:954-9 [74].

Purpose: To determine if a limited number of clinical criteria can reliably identify significant intracranial injuries in blunt trauma victims without missing any significant cases.

Methods: Clinicians assessed the presence or absence of candidate criteria on 13,728 consecutive blunt trauma patients for whom computed head tomography was ordered. Clinicians completed their assessments prior to obtaining imaging results. CT imaging results were reviewed to determine which patients had intracranial injuries. Recursive partitioning was used to identify which candidate criteria reliably predicted injury.

Results: The study enrolled 13,728 patients, including 917 with clinically important intracranial injuries. Recursive partitioning identified eight criteria that were highly associated with intra-cranial injury. These criteria include: 1 - evidence of significant skull fracture, 2 - scalp hematoma 3 - neurologic deficit, 4 - altered level of alertness, 5 - abnormal behavior 6 - persistent vomiting, 7 - coagulopathy, 8 - age 65 years or greater. This rule exhibits 98.3% sensitivity (C.I.: 97.2 – 99.0), a 99.1% negative predictive value (C.I.: 98.5 – 99.5), and a specificity of 13.7% (C.I.: 13.1 – 14.3). Implementation of this rule would have identified all but 16 of 917 patients having clinically important ICI, and would have correctly classified 1,752 (12.9%) patients as “low risk.” Follow-up evaluations, performed on 1,266 patients who did not undergo computed tomography during their initial presentations, reveal that a small minority of these patients ultimately receive cranial imaging. However, none of the follow-up cases required hospitalization or neurosurgical intervention, and there were no cases of missed intracranial injuries or death among this cohort.

Conclusions: We found that a limited number of clinical criteria can reliably identify significant intracranial injuries in blunt trauma victims. The optimal decision instrument developed in this project could still safely decrease tomographic imaging of blunt head injury victims by more than 12%.

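### The instrument's age criterion is defined two ways, so a 65-year-old with no other criterion is positive in some sections of the protocol and low risk in others

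*Protocol*

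**What the plan says.** The age criterion appears in six places in the protocol, in two forms.

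**Age 65 is a risk criterion (≥65):**
- Section 1, Hypothesis I, lists as a condition for being low risk "8 - Age less than 65 years". A 65-year-old fails it.
- Section 3.1, Phase II results, gives the derived criterion as "age 65 years or greater".
- Appendix C defines the criterion as "Age 65 years or more" and takes it from the available history.

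**Age 65 is not a risk criterion (>65):**
- Section 2, in its account of the derivation study, ends the list of eight criteria with "coagulopathy and age greater than 65 years".
- Section 2, in the instrument proposed for evaluation, has "8 - age greater than 65 years".
- Section 4.3.3, the rule that creates the variable, uses the "date of birth to determine if they are of age greater than 65 years".

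Section 4.3.3 also says that a patient is labelled positive if any criterion is present or cannot be assessed, so low risk requires all eight to be absent. The questionnaire in Appendix B collects date of birth but gives no cut-off and has no yes/no item for age.

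**The concern.** The age cut-off is a decision threshold inside the test being validated. The section that creates the variable labels a group of patients differently from the hypothesis under test. Section 4.3.3 contradicts its own reference: it states >65, then points to Appendix C for precise definitions, and Appendix C says ≥65. Clinicians are introduced to the criteria only through Appendix C, so they read one rule while the database may apply the other.

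Four results depend on the label:
- **Sensitivity** for neurosurgical intervention, with its exact 95% interval, which is the primary outcome (section 4.3.7).
- **Specificity**, because >65 moves uninjured 65-year-olds with no other criterion from false positive to true negative.
- **The true-negative count**, which section 4.3.7.2.1 uses as the number of patients who can forgo imaging.
- **The stopping rule** in section 4.3.10.3, which counts neurosurgical cases labelled low risk and ends the study at 10.

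Both codings can be computed from the recorded dates. If the choice stays open, it can be made after it is known which coding produces a miss.

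**Working it through.** **1. The two wordings applied to one patient.** Take a patient aged 65 in completed years with none of the other seven criteria.

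| Place | Wording | Label |
|---|---|---|
| Section 1, Hypothesis I | low risk needs <65 | positive |
| Section 2, account of derivation | >65 | low risk |
| Section 2, proposed instrument | >65 | low risk |
| Section 3.1, Phase II results | ≥65 | positive |
| Section 4.3.3, coding rule | >65 | low risk |
| Appendix C | ≥65 | positive |

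The split is three to three, and section 2 and section 3.1 describe the same derivation study differently.

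**2. The plan's own sample size.** Inputs from section 3.2: α = 0.05 with α/2 in the F quantile, X = N, target lower limit 0.99. With X = N the exact lower limit reduces to P_L = (α/2)^(1/N), so

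N = ln(0.025) / ln(0.99) = 367.04, rounded up to 368.

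Check: 0.025^(1/368) = 0.99003. At the assumed 1.2% prevalence, 368 / 0.012 = 30,667, which the protocol gives as 31,000. Both figures are reproduced, and neither depends on the age cut-off.

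**3. One changed label.** Suppose one of the 368 neurosurgical cases is a 65-year-old with no other criterion and all others are detected. The exact lower limit for X of N is the 2.5th percentile of a Beta(X, N − X + 1) distribution.

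- Coded ≥65: 368/368, lower limit 99.00%.
- Coded >65: 367/368 = 99.73%, lower limit 98.50%.

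With two or three misses the limit is 98.05% or 97.64%. One label therefore decides whether the 99.0% target is met.

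**4. How many labels could change.** The protocol gives no age distribution, so this is illustration only. Assume 1–2% of patients are aged 65, and the same share of neurosurgical cases:

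- All patients aged 65: 0.01 × 31,000 = 310 to 0.02 × 31,000 = 620.
- Neurosurgical cases aged 65: 0.01 × 368 = 3.7 to 0.02 × 368 = 7.4.

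Only those with none of the other seven criteria change label. If that share is 2–10% of the neurosurgical cases (also an assumption), the expected number of changed neurosurgical cases is 3.68 × 0.02 = 0.07 to 7.36 × 0.10 = 0.7. For scale, sections 2 and 3.1 report that 16 of 917 important injuries (1.7%) had no criterion in the derivation study, and section 2 adds that none of the 16 needed neurosurgery.

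**The case against.** Several stronger readings are tempting, and the protocol does not support them.

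- **That the study would validate a different rule from the one derived.** A reader could infer this from section 3.1 against section 4.3.3. But section 2 describes the same derivation with >65. Which cut-off was really derived cannot be settled from the protocol. For the same reason one cannot simply order a switch to ≥65: if the derivation used >65, that would create the mismatch it was meant to remove.
- **That 4 to 7 neurosurgical cases are at stake.** That figure counts every 65-year-old. Under the any-criterion rule, only those free of the other seven change label, and the expected number is then probably below one.
- **That the comparison with the Canadian rule is biased.** The Canadian criterion is stated as ≥65. Two rules with different cut-offs are each assessed as defined, and a difference between them is not bias in itself.
- **That taking age from history contradicts taking it from date of birth.** This is weak, since date of birth can be part of the history. It only needs aligning.

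Three further objections are fair. The protocol does not mention completed years; if exact age were meant, the wordings would differ only on the 65th birthday. The drop to 98.50% follows from any single miss, so it shows how sensitive the result is, not how likely this wording is to cause a miss. And no data are lost, because dates of birth and injury are both recorded and either cut-off can be applied at analysis.

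These points limit the size of the problem but do not remove it. The protocol itself fixes the threshold, and fixes it two ways. That both codings remain available is what leaves room for a choice after the results are seen.

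**Conclusion.** The point stands as an unresolved internal contradiction in the definition of the index test. Three places make a 65-year-old positive, three do not, and one of the latter is the operational coding rule, which conflicts with the hypothesis being tested.

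The effect on specificity and the true-negative count cannot be computed from the protocol. The effect on neurosurgical cases is probably small. It still deserves correction, because the design rests on zero misses in 368 and a single changed label takes the lower limit below its target. This conclusion assumes that age is counted in completed years. The contradiction in wording does not depend on that assumption or on the assumed age shares. The planned numbers, 368 and 31,000, are unaffected.

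**What to change.** Before analysis, and before anyone looks at false negatives by age:

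1. Bring section 1 (Hypothesis I), both statements in section 2, section 3.1, section 4.3.3 and Appendix C to one cut-off. Confirm it against the derivation data and make it consistent with the hypothesis being tested.
2. State in section 4.3.3 that age is completed years from date of birth to date of injury.
3. Make Appendix C name the same source of age as section 4.3.3.

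The cost is a few lines of text, one check of the derivation coding and one line of analysis code. No new data are needed and the sample size stays as it is.
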